**Fig. 1 Fig1:**
[figure not shown]
Participant flow

Unscheduled examinations may be performed under various circumstances. For example, a participant may visit the hospital and undergo dynamic contrast-enhanced CT between surveillance tests because of symptoms such as abdominal pain or hematemesis. We will record and report all such cases of unscheduled visits and examinations.

A patient will be considered a dropout, if that participant 1) withdraws consent, 2) receives liver transplantation without diagnosis of liver cancer, 3) is diagnosed as having malignancies other than liver cancer, or 4) does not take two or more consecutive surveillance tests during the trial. To minimize dropout, we will periodically contact participants to remind them of their next scheduled surveillance and to encourage participation. We will also make efforts to obtain relevant information from patients lost to follow-up; for example, if a patient is transferred to a different hospital after hepatic malignancy is diagnosed through this trial, we will contact the patient and ask for information on the results of follow-up treatment or pathological diagnosis.

### Ultrasonography

Abdominal noncontrast US will be performed using commercially available machines (Pro-Sound Alpha10 or Pro-Sound F75, Hitachi Aloka Medical, Tokyo, Japan; ACUSON S2000, Siemens Medical Solutions, Mountain View, CA, USA; iU22, Philips Medical Systems, Best, The Netherlands) with 5-MHz curved-array transducers. Instead of designating specific investigators to perform surveillance US for this trial, we will perform surveillance US as in our current clinical practice. At our institution, surveillance US is performed by well-trained hepatology fellows. They are trained before they start practicing abdominal US, and during the first month of practice, they perform US under the guidance and supervision of faculty members. In performing US, operators follow the guidelines of the Korean Society of Ultrasound in Medicine [31].

### MRI

MRI will be performed using four 3.0-T systems (MAGNETOM Trio Tim, Siemens Healthcare, Erlangen, Germany; Prisma Fit, Siemens Healthcare; Discovery MR 750, GE Healthcare, Milwaukee, WI, USA; Ingenia CX, Philips Healthcare, Best, the Netherlands). All images will be obtained in the transverse plane with a field of view of 44 cm × 33 cm or 40 cm × 30 cm, according to the patient’s body size. After obtaining the localizer images (scanning time: ~ 20 s), T1-weighted images will be obtained by dual-echo T1-weighted gradient-recalled echo (GRE) (~ 20 s) and three-dimensional volume interpolated GRE (~ 20 s) sequences. T2-weighted images will be acquired by single-shot fat-suppressed navigator-triggered fast or turbo spin echo sequence (3–4 min, depending on the regularity of respiration and patient compliance) and by single-shot breathhold fast or turbo spin echo sequence with a long echo time of 140–150 msec (scanning time: ~ 20 s). We will also obtain free breathing or respiratory gated diffusion-weighted images with b-values of 50, 400, and 800 s/mm^2^ (2–4 min), respectively. The apparent diffusion coefficient will be automatically calculated and displayed as a corresponding map. The total scanning time will be approximately 7–10 min, depending on the MRI machine, and the regularity of patients’ respiration and their compliance. Details regarding MRI parameters are presented in Table 1.

**Table 1 Tab1:** Parameters of surveillance noncontrast MRI

Sequence	Scanner^a^	Matrix Size	ST (mm)	Gap (mm)	TR (msec)	TE (msec)	FA (°)
Dual-echo T1-WI GRE	Magnetom (2D)	256 × 192	6	1.2	150	1.23/2.46	65
	Ingenia (3D)	278 × 256	2	0	3.2	1.15/2.30	10
	Discovery (3D)	320 × 256	2	0	3.9	1.12/2.35	12
	Prisma (3D)	320 × 256	2	0	9	1.34/2.73	9
T1-WI 3D GRE	Magnetom	256 × 192	2	0	2.54	0.95	13
	Ingenia	256 × 282	2	0	3.1	1.42	10
	Discovery	320 × 288	2	0	4.2	1.9	12
	Prisma	320 × 256	2	0	2.68	1.08	9
T2-WI with fat saturation	Magnetom	256 × 192	4	1	466	96	150
	Ingenia	320 × 212	4	1	758	80	90
	Discovery	320 × 256	4	1	2800	80	90
	Prisma	320 × 182	4	1	620	105	107
T2-WI with long TE	Magnetom	320 × 168	4	1	450	148	150
	Ingenia	320 × 186	4	1	522	150	90
	Discovery	320 × 224	4	1	840	150	90
	Prisma	320 × 208	4	1	600	153	98
DWI	Magnetom	128 × 96	6	1	5200	67	90
	Ingenia	128 × 128	5	1	4848	55	90
	Discovery	128 × 80	5	1	4800	51	90
	Prisma	140 × 112	5	1	5500	63	90

^a^Full scanner names are Magnetom Trio Tim (Siemens), Ingenia CX (Philips), and Discovery MR750 (GE), and Prisma Fit (Siemens)

*2D* Two-dimensional, *3D* Three-dimensional, *ST* Slice thickness, *TR* Repetition time, *TE* Echo time, *FA* Flip angle, *GRE* Gradient-recalled echo, *DWI* Diffusion-weighted imaging

### Imaging evaluation

Surveillance US findings will be interpreted and reported by the well-trained hepatology fellows. During US, a suspicious nodule on US is defined as a newly appearing nodule > 1 cm. Diffuse infiltrative lesions with or without suspected tumor in the vein are also considered suspicious for HCC. Simple cysts or lesions that have been previously diagnosed as benign lesions, such as hemangiomas, and show no significant interval change are not considered suspicious, irrespective of the size.

Surveillance noncontrast MRI will be evaluated by one of three board-certified abdominal radiologists ([name]). At noncontrast MRI, a suspicious nodule is defined as a newly appearing nodule > 1 cm that shows at least one of the following imaging features: T1 hypointensity, T2 hyperintensity, diffusion restriction, nodule-in-nodule pattern (mosaic appearance), iron sparing, heterogeneous fatty changes, blood products, or definite tumor diameter increase. Diffuse infiltrative lesions with or without a suspected tumor in the vein are also considered suspicious. Simple cysts, hemangiomas, and lesions that have been previously diagnosed as benign lesions are not considered suspicious, irrespective of the size.

Diagnostic dynamic contrast-enhanced CT or MRI will be evaluated and reported using the Liver Imaging Reporting and Data System (LI-RADS) [30], by one of the three board-certified abdominal radiologists ([name]). LI-RADS version 2014 was used at our institution until June 2017; after that date, we have been using LI-RADS version 2017.

### Reference standards

The final diagnosis will preferably be determined based on histopathologic findings through surgery (when appropriate, according to the practice guidelines) or biopsy. When histopathologic diagnosis is not possible (i.e., if a patient refuses or cannot tolerate an invasive procedure) or when invasive biopsy is deemed to do more harm than good (i.e., a patient with radiologically definite HCC at an advanced stage in whom curative treatment is not indicated), radiologic diagnosis will be applied. For radiologic diagnosis, lesions categorized as LR-5, LR-5 V (LR-TIV in LI-RADS version 2017), or LR-M according to the LI-RADS diagnostic algorithm will be diagnosed as hepatic malignancies [30].

### Outcomes

The primary endpoints are detection rates of very early or early stage HCC, stage distribution at the initial diagnosis, and false positive referral rates. The detection rate is defined as the number of patients whose liver cancer is detected using a given surveillance modality divided by the total number of patients under surveillance with the modality, expressed as a percentage. Very early stage cancer is defined as a single tumor < 2 cm, and early stage cancer is defined as a single tumor < 5 cm or up to three tumors < 3 cm [7, 8]. Surveillance is considered a failure when patients are diagnosed at late (i.e., intermediate or advanced) stages. The false positive rate is defined as the number of positive tests that are eventually confirmed as negative on subsequent dynamic imaging and/or pathologic examination divided by the total number of tests in a specific surveillance modality, expressed as a percentage. The secondary endpoints are 5- and 10-year overall survival rates. We will report these long-term outcomes in separate papers.

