### Sample size

Based on the past prevalence of HCC in at-risk patients undergoing surveillance in our institution, we anticipate that the prevalence of HCC in our study cohort will be approximately 18% over a study period of 5 years. The diagnostic sensitivities of noncontrast US and noncontrast MRI are expected to be 60% and 90%, respectively [10, 25]. Based on these expected prevalence and sensitivities, and an anticipated dropout rate of 15%, we calculated that we would need a sample size of 416 patients (208 for each group) to yield 80% power (1 minus the probability of a type II error) to detect a significant difference in detection rate between the noncontrast US and noncontrast MRI arms, with a two-sided type I error of 5% [32].

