### Statistical analysis

Both intention-to-treat (considering all patients as randomized irrespective of the surveillance test they actually receive) and per-protocol analyses will be performed. The detection rate, stage distribution, and false positive rates will be compared between the noncontrast US and noncontrast MRI arms using the Fisher’s exact or chi-square test. To compare the variables between the two groups, we will use the independent t-test or Mann-Whitney U test for continuous variables and the chi-square or Fisher exact test for categorical variables. If necessary, we will perform logistic regression analysis to determine the independent associations between variables. Survival will be compared using the Kaplan-Meier methods with log-rank test. Cox proportional hazard regression will be performed to determine the independent associations between survival and potential explanatory variables.

Subgroup analyses will be performed. We will perform the analyses after excluding patients in whom liver cancer is diagnosed at their first MRI surveillance tests following the negative US prior to study enrollment. We will compare the tumor stages between patients diagnosed at the first tests and those diagnosed at later tests among patients undergoing noncontrast MRI surveillance. These analyses are intended to examine and exclude the possibility that the tumors already exist but are missed by the noncontrast US test prior to enrollment. In addition, we will examine the effects of the quality of the echogenic window to the liver and the parenchymal nodularity on our primary endpoints. Furthermore, we will explore the additional benefit of serum AFP testing in conjunction with noncontrast US or noncontrast MRI for the detection of early stage HCC. Two-sided *p*-values < 0.05 are considered statistically significant. All statistical analyses will be performed using the SAS 9.2 software package.

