## Discussion

Our goal is to determine whether surveillance with noncontrast MRI can further improve the overall survival of patients at high risk of developing HCC, compared with surveillance using noncontrast US. To achieve this goal, we have designed this study as a two-arm randomized trial. However, no previous study has investigated the performance of noncontrast MRI in detecting HCC patients at early stages in a surveillance setting, although one study examined the diagnostic performance of noncontrast MRI to detect and diagnose HCC in a limited cohort of patients, primarily at very early or early stages [25]. Thus, we first set our primary endpoints as detection rate of early-stage HCC and false positive rate. At long-term follow-up of the current study cohort, we may observe a significant difference in overall survival between the two arms; if this is not possible, an appropriate sample size could be calculated based on the results of current trial for a future large-scale, multicenter trial.

We will perform surveillance every 6 months using both serum AFP and imaging tests, since the combined use of noncontrast US and AFP is recommended for surveillance in many practice guidelines published in Asia, including Korea [5, 6]. Inclusion of AFP may be a confounding factor in comparing the two imaging modalities. However, it would be unethical to exclude serum AFP testing from HCC surveillance for the sake of a clinical trial because the current evidence points to noncontrast US combined with serum AFP as the most effective surveillance strategy [34]. One advantage of this study design, however, is that this trial will allow us to assess the benefit of AFP performed in addition to US or MRI in HCC surveillance, by examining the proportion of cases where early-stage HCC is detected by AFP elevation with negative US or MRI results.

We will not designate experienced radiologists specifically for our surveillance US. Instead, as is currently practiced at our institution, well-trained hepatology fellows will perform surveillance US. In real-world clinical settings, many patients receive their surveillance US examinations in local community clinics instead of tertiary care centers, often by less-experienced US operators with less-than-optimal protocols or equipment [35]. It would be unrealistic to have all surveillance US examinations performed exclusively by a limited number of highly experienced operators.

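### Three unranked primary endpoints are each tested at two-sided 0.05, so the chance of at least one false positive primary result is about 8 to 14%, and the Discussion lists only two of them

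*Protocol article*

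**What the plan says.** The Outcomes section lists three primary endpoints in one sentence, without rank: "The primary endpoints are detection rates of very early or early stage HCC, stage distribution at the initial diagnosis, and false positive referral rates". The abstract gives the same three.

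The Statistical analysis section compares all three between arms by Fisher's exact or chi-square test. On analysis sets it says: "Both intention-to-treat (considering all patients as randomized irrespective of the surveillance test they actually receive) and per-protocol analyses will be performed". Neither set is named as deciding. The threshold is general: two-sided p-"values < 0.05 are considered statistically significant".

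The Sample size section sets 80% power "to detect a significant difference in detection rate between the noncontrast US and noncontrast MRI arms", "with a two-sided type I error of 5" percent. It gives no power or error statement for the other two endpoints.

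The Discussion describes the primaries differently: "Thus, we first set our primary endpoints as detection rate of early-stage HCC and false positive rate". Stage distribution is absent. The abstract's discussion and the last paragraph of the main Discussion treat earlier detection and fewer false referrals as separate conclusions, each of which the trial is expected to answer.

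**The concern.** Three tests, each able to support a primary claim on its own, give three chances of a false positive. Nothing in the text makes the claims conditional on one another: there is no order, no shared alpha and no requirement that all three succeed. The overall error rate for the primary family is therefore above the 5% that applies to a single test.

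The trial is also open-label, and its own text disagrees on whether stage distribution is primary. If the detection rate is not significant but stage distribution or false positive referral is, a reader of the results could not tell from this document whether the trial met its primary objective.

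**Working it through.** **Inputs from the protocol article.** Three primary endpoints (Outcomes). Two analysis sets and p < 0.05 two-sided (Statistical analysis). HCC prevalence 18%, sensitivities 60% and 90%, dropout 15%, 208 per arm, 80% power, two-sided alpha 5% (Sample size). At least 10 surveillance rounds (Participant flow).

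**Step 1. Reproduce the plan's own figure.** Two-proportion formula, pooled variance under the null, mean proportion 0.75:

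n = [1.960 × √(2 × 0.75 × 0.25) + 0.842 × √(0.24 + 0.09)]² / 0.30² = 31.5, rounded up to 32 HCC cases per arm.

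32 / 0.18 = 177.8, and 177.8 / 0.85 = 209.2 per arm, against the stated 208. With 208 × 0.85 × 0.18 = 31.8 cases per arm, power is 80.4%. So 416 reproduces as one comparison at the full 5%, with nothing reserved for the other two primaries.

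**Step 2. Three tests, independent.** 1 − 0.95³ = 14.3%. For the Discussion's two primaries, 1 − 0.95² = 9.75%.

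**Step 3. Three tests, correlated.** The document gives no correlation, so a range is shown (simulated normal test statistics, equal pairwise correlation):

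| Correlation | At least one false positive |
|---|---|
| 0 | 14.3% |
| 0.3 | 13.7% |
| 0.5 | 12.5% |
| 0.7 | 10.9% |
| 0.9 | 8.4% |

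**Step 4. Null simulation of the planned tests.** 40,000 trials with 208 per arm, 18% HCC and 10 tests per patient. Assumptions not in the document: HCC stages split 35% very early, 40% early and 25% late; 3% false positives per test, independent within patient; 15% of patients excluded at random from the per-protocol set. Each single test rejected in 4.8 to 5.2% of trials. At least one of the three ITT tests rejected in 13.7%.

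**Step 5. Adding the per-protocol set.** In the same simulation, at least one of all six tests rejected in 18.5%. With normal statistics and ITT/per-protocol correlation of 0.85 to 0.95, the six-test figure is about 18 to 21% for unrelated endpoints, 16 to 18% at endpoint correlation 0.5 and 11 to 12% at 0.9. The second set thus adds roughly 2 to 6 points.

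**Step 6. Alpha and power under an adjusted threshold.** 0.05 / 3 = 0.0167. Three independent tests at that level give 1 − (1 − 0.0167)³ = 4.9%. On the Step 1 method, power at 31.8 cases per arm is 65%. Restoring 80% would take 43 cases per arm: 43 / 0.18 / 0.85 = 281.05, so 282 per arm or 564 in all.

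**The case against.** *A statistical analysis plan may settle it.* Order and adjustment are often left to that document, and a sentence on p < 0.05 can be no more than a nominal convention. This limits the point to what the article fixes, but the article does fix something: equal primaries and one flat threshold. The mismatch between Outcomes and Discussion lies in the article's own text, although it is a small wording matter.

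*Earlier detection and fewer false referrals are different questions.* It is arguable that they need no common error rate. On that view 14.3% is not the error of any single conclusion. However, the article calls all three primary, and early detection rate and stage distribution bear on the same question.

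*The error counts both directions.* This is correct. For false results favoring MRI only, three independent tests give 1 − 0.975³ = 7.3%, against 2.5% for one test (taking stage as a directional comparison).

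A reader might infer more than the document supports:

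- *The trial breaches its stated 5%.* It does not. The Sample size section claims 5% for the detection-rate comparison only, and testing that at 0.05 honors it.
- *The error is 26.5%, from six tests.* 1 − 0.95⁶ = 26.5% treats heavily overlapping sets as independent. It is not a realistic figure, nor is it an upper bound.
- *The claim of better early detection alone carries 9.8%.* That assumes independence and counts both directions. For false MRI superiority it is 1 − 0.975² = 4.9%.
- *The headline can be picked freely afterwards.* The detection rate is listed first throughout and is the only comparison with a power statement; ITT is named first and defined. Running per-protocol alongside it is routine.
- *The trial was sized on early-stage detection.* The Sample size section says detection rate without that qualifier, and its arithmetic compares sensitivities.

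**Conclusion.** The point holds in a limited form. Followed as written, the three ITT primary tests give about an 8 to 14% chance of at least one false positive. This rests on all three null hypotheses being true, each test holding its own 5%, and any one result being enough for a primary claim. The last condition is not stated outright; it follows from the absence of any linking rule and from the separate conclusions drawn. Had the plan required all three to succeed, there would be no inflation.

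The three endpoints account for most of the excess. The per-protocol set is a minor addition, and matters only if a per-protocol result could carry a claim. The 5% stated for the detection-rate comparison is not itself in error. The plan should be changed, but the remedy is wording and the design is not invalidated.

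**What to change.** Before the primary analysis (the article reports that follow-up is still ongoing):

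1. State that ITT decides and that per-protocol is a sensitivity analysis.
2. Choose one rule for the three ITT tests. *Either* a fixed order with the detection rate first at two-sided 0.05, each later endpoint tested at 0.05 only if those before it succeed; *or* Holm across the three, which holds 5% under any correlation.
3. Make Outcomes and Discussion give the same list of primaries, and say whether the detection rate in Sample size is the early-stage one.

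Cost: no extra patients need be enrolled. Under a fixed order, stage distribution and false positive referral cannot be claimed as primary findings if the detection rate fails. Under Holm, the smallest of the three p-values must be below 0.0167. Power for the detection comparison at that step is about 65% instead of 80% at N = 416, on the protocol's sensitivity-based method; it is higher if another endpoint has already been rejected.

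One caution on choosing the fixed order. Outcomes defines the detection rate over all patients under surveillance, which gives 0.18 × 0.60 = 10.8% against 0.18 × 0.90 = 16.2%. Power for that comparison at two-sided 0.05 is only about 32% with 177 evaluable per arm and 36% with 208. That is a separate sample-size question, but it affects how often the first step would be passed and should be settled before the order is fixed.

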### Participant flow

A trained research nurse will introduce the trial to potentially eligible patients, who will be provided with detailed information about the trial. They will then be able to have an informed discussion with participating physicians, who will obtain written consent if the patients agree to participate in the trial. Enrolled participants will be randomly assigned to either abdominal US or noncontrast MRI in addition to serum AFP testing for HCC surveillance (Fig. 1). They will be evaluated by at least 10 rounds of surveillance tests at 6-month intervals (with a variation of ±1 month allowed). The first surveillance test will be performed 6 months after the most recent imaging study showing no evidence of hepatic malignancy. If a new lesion detected during US or MRI surveillance is suspected to be malignant according to the predefined criteria (see Imaging evaluation section) or if the serum AFP level is elevated in an increasing trend for two consecutive tests, dynamic contrast-enhanced CT will be performed [6, 30]. The reference value for AFP is less than 9 ng/mL at our institution. Additional dynamic liver MRI may be performed at the discretion of clinicians. If the surveillance test result is determined to be a false positive by subsequent tests, the patient will return for the next scheduled surveillance test. If a patient is confirmed as having a hepatic malignancy, the patient will receive standard treatment according to the guidelines [5–8]. We will continue follow-up of treated patients for at least 5 years to obtain and compare the overall survival rates.

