### Randomization and blinding

A research nurse will assign participants into either the noncontrast US group or the noncontrast MRI surveillance group according to a computer-generated randomization list. The randomization sequence will be created using SAS 9.2 (SAS Institute, Inc., Cary, NC, USA) statistical software by an investigator with no clinical involvement in the trial, with a 1:1 allocation using a random block size of 4. Only the research nurse will have knowledge of the randomization sequence. However, once investigators obtain a participant’s consent and the research nurse assigns him or her to the noncontrast US or noncontrast MRI group, the participant and investigators will inevitably be aware of the surveillance assignment at the time of the initial surveillance examination. Therefore, blinding of participants and investigators is not possible for this trial.

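### The false-positive referral rate is counted per test, with about 10 tests per randomised patient, but is compared by tests that assume independent observations, so its nominal 5% p-value is not valid in general

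*Protocol article*

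**What the plan says.** The Outcomes section gives the endpoint primary status: "The primary endpoints are detection rates of very early or early stage HCC, stage distribution at the initial diagnosis, and false positive referral rates". It then sets the unit of counting. For the numerator: "The false positive rate is defined as the number of positive tests that are eventually confirmed as negative on subsequent dynamic imaging", with pathology as a further means of confirmation. The denominator is all tests done with the modality: "divided by the total number of tests in a specific surveillance modality, expressed as a percentage". The detection rate in the same section is instead counted per patient.

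Participant flow sets the number of tests per patient: "They will be evaluated by at least 10 rounds of surveillance tests at 6-month intervals". It also lets one patient contribute more than one false positive: "If the surveillance test result is determined to be a false positive by subsequent tests, the patient will return for the next scheduled surveillance test".

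Randomization and blinding assigns patients, not tests, "with a 1:1 allocation using a random block size of 4".

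Statistical analysis names the comparison: "false positive rates will be compared between the noncontrast US and noncontrast MRI arms using the Fisher’s exact or chi-square test", with two-sided significance at 0.05. No method for repeated tests within a patient is named. Logistic regression is mentioned only as an option and is not described as clustered.

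**The concern.** Fisher's exact and chi-square tests on a 2x2 table need one independent observation per count. Here the table would hold some 1,770 to 2,080 tests per arm from at most 208 randomised patients per arm. If some patients are persistently prone to false alarms, the tests carry less information than their number suggests, and the usual standard error is too small.

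The protocol itself gives a reason to expect such persistence. It plans to examine how the echogenic window and parenchymal nodularity affect the primary endpoints, and both are largely stable features of a patient. The Background also lists patient characteristics among the things that affect ultrasound results.

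At stake is one of the trial's stated conclusions: whether MRI surveillance leads to fewer false referrals than ultrasound. That statement will rest on this p-value.

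This is not a detail left to a fuller plan. The article states the unit, the number of repeats and the test, and the three do not fit together.

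**Working it through.** **The plan's own figure.** The article gives no expected rate, power or correlation for the false-positive endpoint. Its only sample-size figure, 416 (208 per arm), concerns detection. Comparing 60% with 90% at two-sided 5% and 80% power needs 31.5 HCC cases per arm, or 32 rounded up. Then 31.5 / 0.18 / 0.85 = 206 per arm (412 in total), or 32 / 0.18 / 0.85, rounded up, = 210 per arm (420 in total). That is close to 416, but it says nothing about the precision of the false-positive comparison.

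**Inputs from the protocol article.** 208 patients per arm; 15% dropout, so 208 x 0.85 = 177 per arm; at least 10 rounds per patient, so m = 10; two-sided 5% level.

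**Tests entering the table.** 177 x 10 = 1,770 per arm, or 208 x 10 = 2,080 without dropout.

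**Assumed input.** The intra-patient correlation (ICC) is not in the document, so a range is shown.

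**Formulae.** Design effect DE = 1 + (m - 1) x ICC = 1 + 9 x ICC. The naive standard error is too small by the factor sqrt(DE). True type I error = 2 x [1 - Phi(1.96 / sqrt(DE))]. Effective tests per arm = 1,770 / DE.

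| Assumed ICC | DE | sqrt(DE) | True type I error | Effective tests per arm |
|---|---|---|---|---|
| 0 | 1.00 | 1.00 | 5.0% | 1,770 |
| 0.01 | 1.09 | 1.04 | 6.1% | 1,624 |
| 0.02 | 1.18 | 1.09 | 7.1% | 1,500 |
| 0.05 | 1.45 | 1.20 | 10.4% | 1,221 |
| 0.10 | 1.90 | 1.38 | 15.5% | 932 |
| 0.20 | 2.80 | 1.67 | 24.2% | 632 |

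**Simulation of the formula.** Beta-binomial data were generated with 177 patients per arm, 10 tests each, 20,000 replicates and assumed false-positive rates of 1, 3, 5 and 10%. The naive chi-square test gave 6.7 to 7.3% at ICC 0.02, 10.1 to 10.3% at 0.05, 15.2 to 15.8% at 0.10 and 23.7 to 24.4% at 0.20. A patient-clustered variance gave 4.6 to 5.3% in every scenario. This confirms the formula but says nothing about which ICC is true.

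**The opposite limit.** Suppose each patient can have at most one false positive. With an underlying per-test rate p, the chance that a patient has one is P = 1 - (1 - p)^10. The true variance of the patient's count is P(1 - P). The naive test assumes 10 x (P/10) x (1 - P/10) = P(1 - P/10). The ratio (1 - P) / (1 - P/10) takes the place of DE.

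| p | P | Variance ratio | Type I error, formula | Type I error, simulation |
|---|---|---|---|---|
| 1% | 0.096 | 0.913 | 4.0% | 4.0% |
| 3% | 0.263 | 0.757 | 2.4% | 2.5% |
| 5% | 0.401 | 0.624 | 1.3% | 1.3% |

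The naive test is then too cautious and loses power. The patient-clustered variance stays at 5.1 to 5.3% here as well.

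**The case against.** The strongest reply is that the direction is not known. The Imaging evaluation section requires a suspicious nodule to be new, and takes lesions already established as benign out of consideration (for ultrasound, provided they have not changed materially). A lesion that has been worked up is therefore largely barred from triggering again, which works against positive correlation. This stands, and it is why the range must include zero and negative correlation. It does not rescue the planned test. The rules limit repeats of the same lesion, not new nodules in the same liver, and a negative correlation also invalidates the p-value, only in the conservative direction.

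The upper ICC values are also weakly grounded. If the per-test rate were 3 to 5% (an assumption), ICC 0.20 would mean that a patient with one false positive has a chance of p + ICC x (1 - p) = 22 to 24% on any other test, roughly five to seven times the base rate. Nothing in the document supports so strong a clustering. This stands too, and 24% is the end of an illustrative range, not an expectation.

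A reader might infer that the error rate is known to be inflated, or that published confidence intervals will be wrong. The document supports neither. It gives no ICC, and it plans no interval for this endpoint; only an interval computed under the same independence assumption would share the fault. Nor does the argument rest on AFP, because the text does not say whether a referral triggered by AFP alone counts as a false positive.

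Finally, the article condenses a longer plan, which may treat the repeated tests properly. That lowers the certainty that the naive test will be run, but the test that the article does name is the wrong one for the unit it defines.

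**Conclusion.** The point holds as a mismatch between unit of analysis and test. A per-test primary endpoint, with about 10 tests per randomised patient, is to be compared by methods that need independent observations, so the 5% level is not assured.

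The size is uncertain. It runs from about 1.3% in the conservative limit (underlying rate 5%, at most one false positive per patient), through 5% at no correlation, to about 24% at an assumed ICC of 0.20. Persistent patient features make some positive correlation plausible, and an ICC of 0.01 to 0.05 would give 6 to 10%. Known inflation cannot be claimed.

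The figures assume 10 tests for every patient; actual numbers will vary with dropout and HCC diagnosis. The estimated rate, the randomisation and the data collection are not affected. The correction belongs to the analysis stage and should be made, but the defect does not undermine the trial's design.

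**What to change.** Keep the per-test false-positive rate as the estimate. For this endpoint, replace the Fisher's exact or chi-square comparison with one that treats the patient as the cluster: a GEE logistic or Poisson model with robust standard errors, or a patient-level bootstrap or permutation test. Any of these allows for correlation in either direction, so the ICC need not be known in advance.

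As a supportive result, report the proportion of patients in each arm with at least one false-positive referral, compared by chi-square. That comparison has one observation per patient and matches the unit of randomisation. It ignores differences in the number of rounds completed, so it should accompany the per-test rate and not replace it.

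The cost is one line of analysis wording and a few lines of code, with no new data. The p-value may become less favourable if false positives cluster within patients.
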